**Fig 3 pone.0357117.g003:**
[figure not shown]
Data flow chart.

Data will be used during the active project phase (01 January 2025–30 June 2028). In addition, data access will be maintained for up to 18 months after the end of the project to allow for additional analyses in the context of the peer-review and publication process. Subsequently, datasets will be securely archived in encrypted form and stored for 10 years in accordance with Good Practice for Secondary Data Analysis guidelines, after which they will be permanently deleted [27].

For the PE, quantitative data from participating patients will be collected using paper-based questionnaires distributed by the PN and subsequently entered into a Research Electronic Data Capture (REDCap) database after completion. Alternatively, participants may complete the questionnaires directly via a secure link to the REDCap database used within the PRIMA study. All questionnaires are pseudonymized at the patient level using participant-generated pseudonyms; no directly identifiable personal or medical information is accessible to the study team. Information on the reliability and validity of the questionnaires used in the target population is provided in Table 3. Duplicate entries will be excluded. Participating PNs will receive standardized training on instructing participants in questionnaire completion. Activity documentation is likewise pseudonymized at the patient level using the same pseudonym for matching purposes. Quantitative data documented by the practice teams are recorded anonymously. Qualitative data will be collected through individual and group interviews conducted either in person or via Zoom. Interviews will be audio-recorded and transcribed verbatim. All interviewers will receive training prior to data collection. Transcripts will be pseudonymized, and all identifying information will be removed during the pseudonymization process. Audio recordings will be retained until completion of the analyses to allow clarification of potential transcription uncertainties. All transcripts will be reviewed by the respective interviewers for accuracy. In addition, qualitative activity documentations will be collected from the practice teams for three selected workdays. Participants will create these themselves in the form of written documents or audio files, and submit them to the scientists from the Institute of General Practice and Interprofessional Care, Tuebingen (IAIV). All qualitative activity logs will be transcribed and pseudonymized if necessary, using the same procedure as for the interviews.

All study data will be stored for 10 years after completion of the analyses in accordance with international standards for good scientific practice. Access to personal information will be restricted to authorized study personnel only.

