### Recruitment

#### Intervention group – participating practices, PNs and patients.

Participating practices were recruited between January and December 2025, while information about the PRIMA project had already been shared in the two months leading up to the project start. Recruitment was conducted by the Association of SHI Physicians of Baden-Württemberg (KVBW) through two sequential steps. First, postal letters were sent to a sample of randomly selected practices, followed by information and outreach via email to a further randomly selected sample of practices in the federal state of Baden-Württemberg, Germany. PNs employed in PRIMA were recruited by the practices themselves or via the KVBW. All PNs participating in PRIMA must have completed a three-year vocational training program as nursing professional (*Altenpfleger:in*, *Gesundheits- und Krankenpfleger:in* or *Pflegefachfrau/-mann*) and possess either an academic postgraduate qualification in nursing or at least five years of professional experience in nursing, preferably across different care settings. Alternatively, nurses who have obtained an academic qualification in nursing, such as a bachelor’s or master’s degree with a specialization in Advanced Nursing Practice could be employed. Patients eligible for participation were identified in a stepwise approach using a combined data-driven approach and clinical judgement by the GP and the respective practice team based on the inclusion and exclusion criteria. All study participants are recruited between 1 January 2026 and 30 September 2026. Eligible patients are informed about the study during routine consultations. Written informed consent is obtained by the treating GP and forwarded to KVBW prior to participation using a standardized consent form approved by the ethics committee. Where applicable, consent must be provided by a legal guardian or authorized representative.

For the PE, all study participants with the capacity to provide informed consent are invited by the PN to participate in the surveys of the PE. Recruitment of the practice teams, patients as well as their relatives and collaborators for the qualitative case studies is guided by the scientists from Institute of General Practice and Interprofessional Care, Tuebingen (IAIV) in a selective sampling approach guided by the principle of information power. Informed consent was obtained from all participants in the PE [25].

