**Micro Level (patients and their relatives)**						
Quality of life	EQ-5D-5L [50–53]	–	X	–	x	P
Self-Efficacy	Self-Efficacy-Scale (SES6G) [54]	–	X	–	x	P
Subjective symptoms and treatment satisfaction	Measure Yourself Medical Outcome Profile (MYMOP) [55,56]	–	X	–	x	P
Satisfaction with care by PN	Nurse Practitioner Satisfaction Survey (NPSS) [57,58]	–	–	–	x	P
Patients assessment of chronic illness care	PACIC short [59–63]	–	x		x	P
Patients’ experiences of the new model of care	Qualitative Case Study	–	–	–	x	P/R

B: Baseline, Start of NP in Practice Teams, T0: Start of Intervention, T1: Mid Intervention, T2: End of Intervention; ICAP: Interactive –Constructive-Active-Passive; P: Population, PT: Practice Team; PN: Prima nurse, C: collaborators; R: relatives

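### For the end-of-intervention NPSS, the nurse being rated invites patients, hands out the paper form and instructs them in completing it, which is likely to bias the ratings upward

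*Protocol article*

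**What the plan says.** Three statements in the protocol article fix the nurse's role in the patient surveys.

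- Invitation (Recruitment, intervention group): all participants able to consent "are invited by the PN to participate in the surveys of the PE".
- Distribution (Data): the paper route uses "paper-based questionnaires distributed by the PN".
- Instruction (Data): "Participating PNs will receive standardized training on instructing participants in questionnaire completion".

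Table 3 lists what patients complete. One row is "Satisfaction with care by PN", measured with the NPSS at T2 only. Another is "Patients assessment of chronic illness care", measured with the short PACIC at T0 and T2.

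The Data section gives two safeguards. The first is online completion: "Alternatively, participants may complete the questionnaires directly via a secure link to the REDCap database". The second is a pseudonym that each participant generates, so that "no directly identifiable personal or medical information is accessible to the study team". The same section says that activity documentation carries the same pseudonym, so that the two can be matched. The intervention section says that the nurse writes up every nurse contact in a work diary.

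Questionnaire data are analysed descriptively, with inferential analyses only exploratory (Process evaluation).

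**The concern.** The NPSS is the only patient questionnaire in Table 3 labelled as a rating of the nurse. The person rated stands at three points between the patient and the answer: the invitation, the handover and the instruction. Patients who depend on the nurse for continuing care may answer more kindly than they otherwise would. Those who are dissatisfied may also be less likely to take or return a form. Both effects push the result in the favourable direction.

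Because the analysis is descriptive and the NPSS is measured once, the raw T2 level is what will be reported. The Discussion expects the findings to inform reimbursement of multiprofessional care, and a favourable satisfaction figure would be read in that light. The limitations cover practice self-selection, dropout and unlinked data sources, but not this source of bias.

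**Working it through.** The plan gives no figure for this point, so there is nothing to reproduce. The check sets the statements side by side, then shows by assumption what sizes are possible.

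**1. Does the nurse's role reach the NPSS?** The statements on invitation, distribution and instruction cover the patient questionnaires in general, and none exempts the NPSS. As written, all three apply to it.

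**2. Do the safeguards remove the problem?**
- The REDCap link helps at the completion step for those who use it. It is an alternative, its expected uptake is not stated, and the nurse still makes the invitation.
- The pseudonym is described as shielding identity from the study team. It is not described as shielding it from the nurse, whose own documentation carries the same pseudonym. The text therefore gives patients no assurance on that side.

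**3. Could a shift be seen afterwards?** The NPSS has no T0 value. A comparison of paper with online answers would be informative, subject to self-selection, but the article does not mention one.

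**4. How does PACIC differ?** With bias b0 at T0 and b2 at T2:

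observed change = true change + (b2 − b0)

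A constant bias cancels. It may grow as patients come to know the nurse, so full cancellation is not assured, but PACIC is less exposed than a single T2 level. Changing the procedure at T2 only would create a difference between b2 and b0.

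**5. Illustrative sizes (every input assumed unless marked).**

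*Courtesy answers:* shift in mean = share answering through the nurse × shift per respondent. With a share of 0.5 to 1.0 and a shift of 0 to 0.3 SD, the mean moves by 0 to 0.30 SD. For example, 0.7 × 0.2 = 0.14 SD.

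*Differential response:* observed satisfied share = p·r1 / (p·r1 + (1 − p)·r2). Here p is the true satisfied share, and r1 and r2 are the response rates of satisfied and dissatisfied patients. With p = 0.70 and r1 = 0.60:

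| r2 | Calculation | Observed share |
|---|---|---|
| 0.60 | 0.42 / 0.60 | 70.0% |
| 0.50 | 0.42 / 0.57 | 73.7% |
| 0.40 | 0.42 / 0.54 | 77.8% |
| 0.30 | 0.42 / 0.51 | 82.4% |

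*Sampling error for comparison:* 95% half-width in SD units = 1.96 × √(DEFF / n), with DEFF = 1 + (m − 1) × ICC. The plan's survey estimate is n = 2,000 and it has 20 practices, so m = 2,000 / 20 = 100. The ICC range of 0.01 to 0.10 is assumed; the plan's 0.01 belongs to the sample size for the primary endpoint.
- ICC 0.01: DEFF = 1.99, half-width 0.062
- ICC 0.05: DEFF = 5.95, half-width 0.107
- ICC 0.10: DEFF = 10.9, half-width 0.145

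The 2,000 includes practice staff, so with fewer patients the real half-widths would be wider. Under these assumptions a shift of 0.1 to 0.3 SD would be of the order of the sampling error or larger, and a larger sample would not remove it. This shows what is possible. It does not estimate the bias in this trial.

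**The case against.** The strongest reply is that the mechanism is partly inferred, that the plan already has safeguards, and that these are descriptive secondary outcomes. Much of this stands, and it rules out several stronger readings.

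- **Forms completed in front of the nurse or handed back to her or him.** A reader might infer this, but the article does not say it. It says only that forms are entered into REDCap after completion. The return route is a detail that a condensed article may leave to the full protocol, so its absence is not the point here.
- **Nurses choosing whom to invite.** The plan invites every participant able to consent. Selective invitation would depart from it.
- **Missing control group.** The process evaluation has none, but usual-care patients have no PRIMA nurse to rate. A control group could not have exposed inflated NPSS scores.
- **PACIC equally affected.** It is not, as step 4 of the working shows.
- **About 2,000 biased responses.** That estimate also counts practice staff, who do not complete the NPSS. Online answers are also less exposed.
- **Instruction has a purpose.** The eligibility table names cognitive impairment, immobility and frailty among the risk features, so withdrawing help could cost response or completeness.

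What remains is that the article positively assigns invitation, distribution and instruction to the person rated. Neither stated safeguard takes the nurse out of the invitation or the instruction.

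**Conclusion.** The point holds for the T2 NPSS. Upward bias is likely. Its direction is a reasoned expectation and its size cannot be derived from the document. The conclusion assumes that the nurse who approaches a patient is the one whose care the patient rates, and that the general statements on distribution and instruction include the NPSS.

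The scope is narrow: one descriptive process-evaluation outcome, on the plan's own survey estimate from fewer than 2,000 patients. A reader might infer that the trial's effectiveness results are compromised. They are not, because the primary endpoint and every other outcome in Table 2 come from claims data. This is a cheap improvement, not a defect in the main evaluation.

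**What to change.** For the T2 NPSS only:

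1. State that the nurse neither instructs on nor collects the form.
2. Give it to patients as a separate sealed form with the existing REDCap link and a prepaid envelope addressed to the evaluating institute. The institute already receives the practice teams' qualitative activity logs directly.
3. Let help with completion come from written instructions or from someone other than the nurse, such as a relative.
4. Report NPSS response by practice, against all enrolled patients able to consent, and by paper versus online.
5. Name the remaining bias as a limitation, since the nurse would still make the invitation.

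Keep the PACIC procedure the same at T0 and T2. T0 data are already being collected under the present procedure, and a change at T2 alone would be confounded with the change score.

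The cost is envelopes, return postage and a line in the nurse training, with no extra staff. Response may be lower or less complete, especially among frail patients. T2 is the end of the intervention and data collection runs to September 2027, so the change is still possible.

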### Safety considerations

No direct medical harms are expected from participation in the PRIMA trial, as the intervention does not involve pharmacological or invasive procedures. Adverse events are not expected to occur in a systematic clinical sense and will therefore not be collected using a structured adverse event reporting system. Potential risks are primarily organizational in nature and may include increased workload or temporary workflow disruptions within participating practices during implementation of the intervention. Participation in the PE is voluntary and not associated with any major risks or burdens. It is possible that participants may feel uncomfortable or burdened during the interviews. If this occurs, they may contact the study leadership. Participants are free to discontinue the interview at any time and to withdraw their consent to participate. If participants find it difficult to answer certain questions in the questionnaires or interviews, these may be skipped. The theoretical risk of data loss cannot be completely ruled out. Any relevant unintended effects reported by participating practices will be documented descriptively and considered in the PE. All identified unintended effects meeting relevance criteria for service delivery will be reported in study publications.

Protocol deviations are primarily relevant at practice level, as the intervention is implemented at cluster (practice) level. Deviations may include partial or delayed implementation of intervention components, such as incomplete integration of the PN. These deviations will be documented descriptively within the PE but will not affect inclusion of practices or patients in the primary effectiveness analyses. At patient level, protocol deviations are not applicable, as outcomes are assessed using routinely collected data independent of patient-level intervention adherence.

### Statistical analysis

#### Matching.

The analysis population comprises patients enrolled in the intervention practices and matched CGs identified from routine data of the Association of SHI Physicians Baden-Württemberg (KVBW) and AOK BW, respectively.

First, matching variables associated with treatment allocation and study outcomes will be defined based on a literature review and expert consultation [28]. Patient-level variables will include sociodemographic and clinical characteristics such as age, sex, and the number of ASE in the pre-observation period. Practice-level variables will include structural characteristics such as practice type and size, approximated by level of care provision or the number of physicians per practice. Additionally, regional indicators such as the density of doctors or the average distance to the nearest GP are considered.

Second, suitable matching methods will be evaluated regarding methodological appropriateness and feasibility using routine data. Given the multilevel structure of the intervention, several approaches will be considered, including Propensity Score Matching, Coarsened Exact Matching, Optimal Full Matching, and cluster-based matching approaches for observational studies [29–32].

Matching will be conducted separately for the two data sources: KV data will be matched at TUM, while AOK BW data will be matched directly by AOK BW. The resulting matched datasets will be assessed for covariate balance and comparability between intervention and CG [33]. The preferred matching approach will be the method achieving the best balance across predefined matching variables and thereby minimizing selection bias.

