### Sample size calculation

For the sample size and power calculation, a baseline rate of 0.20 ASE per patient per year is assumed. In the general population, ASE rates range between 4% and 8% [22]. As the study population consists of patients with chronic conditions selected based on clinical judgement and expected to benefit from enhanced care, a higher baseline rate is expected. Based on published evidence suggesting a 20–40% reduction in ASEs through improved ambulatory care [23], a conservative effect size of 15% is applied.

The study follows a parallel cluster design with 20 practices per arm and approximately 112 patients per practice. This accounts for an anticipated dropout of 20% at practice level and 10% at patient level. The design includes 12 months of pre- and 12 months of post-intervention observation [24]. An intra-cluster correlation coefficient (ICC) of 0.01 is used. Under these assumptions and a two-sided alpha of 5%, the study achieves a statistical power of 82% to detect a 15% reduction in ASE rates.

The PE within PRIMA does not assess a primary endpoint of the study. Therefore, no separate sample size calculation was required for the PE. Instead, the sample size of the PE is determined by the total population of all participant groups included in the PRIMA study and by the methodological approach chosen within the PE sub-projects. For the questionnaire-based quantitative PE, all patients included in the main study as well as all staff members of the participating practices will be included (estimated n = 2,000). To ensure sufficient thematic breadth regarding the research questions – while simultaneously aiming for thematic saturation – a total of 4 practices will be included in the qualitative case studies, leading to about 60 individual interviews (30–60 minutes) with patients, relatives, and practice staff, along with approximately 16 qualitative activity logs. In addition, 4–5 cross-site focus groups (approximately 120 minutes each) with members of the PRIMA teams and stakeholders at interface levels (e.g., care support centers) are planned.

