### Inclusion and exclusion criteria

The predefined inclusion and exclusion criteria used to determine study eligibility are summarized in Table 1.

**Table 1 pone.0357117.t001:** Inclusion and exclusion criteria.

	Inclusion criteria	Exclusion criteria
Patient Level	• Age ≥ 18 years • At least one life-limiting chronic condition reflected by at least two billings of the German chronic care fee (“Chronikerpauschale”, EBM GOP 03220/03221 or equivalent under selective contract) in two of the four quarters preceding study enrolment • Continuous treatment in the participating practice for at least four quarters prior to inclusion • Patients in an unstable phase of chronic disease with ASE related to their chronic condition and/or hospitalizations due to their chronic condition within the past three years • Patients in a stable phase of chronic disease with at least one sign of a high risk of decompensation*	• Estimated life expectancy based on the assessment of the treating GP at the start of the intervention of less than one year (minimum intervention period)
Practice Level	• Practices providing routine care as GPs in the federal state of Baden-Württemberg, Germany • Employment of a nursing professional	• Participation in similar studies

*The risk of decompensation was based on the clinical judgement of the participating GPs in regard of the following aspects: presence of multimorbidity with geriatric characteristics (e.g., immobility, cognitive impairment, or frailty), unfavorable living circumstances (e.g., living alone, partner requiring care, absence of nearby relatives), long-term care dependency (Pflegegrad, care level), frequent changes/dose adaptions in medication, increasing frequency of acute exacerbations or clinically relevant deterioration in vital parameters (e.g., blood pressure, pulse, oxygen saturation, change in weight) indicating disease progression, and reduced ability to participate in or adhere to the care processes.

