### Data

Regarding the effectiveness analysis and economic evaluation, routinely collected healthcare data will be used. Data sources include routine data from KVBW and AOK BW for the reporting period from 01 January 2024–30 September 2027. KVBW includes patient core data, information on participation in the GP-centered care model collected via the study consent form, practice core data, regional indicators, and outpatient claims data. For the subset of AOK BW-insured patients, patient master data, data on outpatient and inpatient care, pharmaceutical prescriptions, remedies and medical aids, long-term care, rehabilitation, sick leave, transportation costs, and domestic help are provided by AOK BW.

Written informed consent will be obtained from all patients participating in the IG prior to inclusion in the study and prior to the transfer and use of routinely collected healthcare data for research purposes. Only routinely collected healthcare data necessary for the predefined analyses will be requested and processed in accordance with the principle of data minimization. KVBW data will be provided as separate datasets for intervention and control groups. A matched CG will be generated from KVBW data based on criteria defined by the evaluator. AOK BW data will be provided as a pre-matched dataset, with matching performed by AOK BW prior to data delivery. Datasets from KVBW and AOK BW will not be linked or merged, as all outcomes are pre-specified to be analyzed within their respective datasets.

Data extraction follows routinely implemented administrative processes and is performed on a quarterly and continuous basis. Data completeness, validity and quality are ensured by standard validation procedures at the respective data providers, and additional plausibility and validity checks are performed at the Technical University of Munich (TUM) data trust office prior to analysis.

Data from both providers are pseudonymized prior to transfer. A double-pseudonymization procedure is applied by the TUM data trust office, replacing study pseudonyms with evaluation pseudonyms to prevent re-identification. The corresponding linkage key is stored under trustee responsibility and is not accessible to the evaluators. Data transfer to the evaluator is performed via secure, encrypted channels and external encrypted storage media, with access restricted to authorized personnel. Fig 3 illustrates the data flow.

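### Best balance on the matching variables does not show that selection bias is minimised, because GP-selected patients and claims controls with equal prior ASE counts can differ in risk

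*Protocol article*

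**What the plan says.** The Matching section names age, sex and the ASE count before the intervention as patient-level variables, and adds practice and regional characteristics. The list is open, to be completed from literature and expert advice. The control group section also names diagnosis and comorbidities. Several matching methods remain candidates, and the choice follows this rule: "The preferred matching approach will be the method achieving the best balance across predefined matching variables and thereby minimizing selection bias".

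Intervention patients enter differently. Under Table 1 they have either had an ASE or a hospitalisation for their chronic condition in the past three years, or are stable with a sign of high risk. On the second route, "The risk of decompensation was based on the clinical judgement of the participating GPs", covering frailty, living situation, care dependency, medication changes, worsening and adherence. The sample size section treats this selection as informative about the outcome: "As the study population consists of patients with chronic conditions selected based on clinical judgement and expected to benefit from enhanced care", a rate above the 4% to 8% of the general population is expected, and "a baseline rate of 0.20 ASE per patient per year is assumed".

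Controls are found in routine data from KVBW and AOK BW. The article does not say that anyone applies the clinical risk criteria to them. Routine data are requested "for the reporting period from 01 January 2024–30 September 2027".

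**The concern.** One year's ASE count is a noisy measure of a patient's underlying rate. If two pools have different mean rates, patients with the same count are expected to move towards different means in the following year. Matching on the count makes the groups look identical before the intervention and lets them separate afterwards, even if the intervention does nothing.

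Balance on the matched count is perfect in every such case, so the rule cannot rank candidate methods on this bias. The primary endpoint is analysed in KVBW data. For that source the Data section lists core data, participation in GP-centred care, practice and regional data, and outpatient claims. Prescriptions, inpatient care and long-term care are listed only for the AOK BW subset, and the two sources are not linked. Several of the features that GPs select on therefore appear to be out of reach when matching for the primary endpoint.

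At stake is the causal reading of the main result, because an effect of 15% is small next to a modest residual difference in risk.

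**Working it through.** **The plan's own figure.** The article gives no figure for residual bias. The nearest is that "the study achieves a statistical power of 82% to detect a 15% reduction in ASE rates". It cannot be reproduced from the printed inputs alone:
- The design effect is 1 + 111 × 0.01 = 2.11, so the effective size is 2,240 / 2.11 = 1,062 per arm.
- With Poisson variance and follow-up data only, z = 0.03 / √(2 × 0.185 / 1,062) = 1.61, and power is Φ(1.61 − 1.96) = 36%.
- Reaching 82% needs a strong pre-post correlation of cluster means (about 0.83 to 0.88), which is not printed and may stand in the full protocol.

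I do not call 82% wrong. I use it below only at face value.

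**Inputs.** From the article: intervention mean 0.20 per year, target rate ratio 0.85, 20 × 112 = 2,240 patients per arm, ICC 0.01. Assumed: gamma-distributed patient rates with shape k, exact matching on a 12-month count, no true effect, and a control-pool mean μ. Here μ is the mean that remains after the other matching variables have explained what they can.

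**Formula.** A patient with count y has expected next-year rate (k + y) / (k/mean + 1). The matched ratio is then the same for every y:

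ratio = (k/μ + 1) / (k/0.20 + 1)

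For k = 0.5 the denominator is 3.5. About 85% of intervention patients have no event, since (0.5/0.7)^0.5 = 0.845. With y = 0 and μ = 0.15, the expected rates are 0.5/3.5 = 0.143 and 0.5/4.333 = 0.115.

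| Residual pool mean μ | Ratio with no effect | A true 0.85 appears as | Chance of a significant benefit |
|---|---|---|---|
| 0.20 | 1.00 | 0.85 | 82% |
| 0.19 | 3.632/3.5 = 1.04 | 0.88 | 60% |
| 0.18 | 3.778/3.5 = 1.08 | 0.92 | 33% |
| 0.15 | 4.333/3.5 = 1.24 | 1.05 | 0.2% |

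The last column uses SE(log ratio) = 0.1625 / (1.960 + 0.915) = 0.0565, the value that 82% power at 0.85 implies.

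**Other settings.**
- At μ = 0.15, k = 0.25 gives 1.19 and k = 1 gives 1.28.
- Matching on 24 months instead of 12 lowers the 1.24 to 1.19 (k = 0.5).
- The whole 15% is hidden when the ratio reaches 1/0.85. That happens at μ between 0.155 and 0.167 for k from 0.3 to 2, about 16% to 23% below 0.20.
- To mimic a 15% reduction, μ would have to lie between 0.240 and 0.267, about 20% to 33% above 0.20.

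**How informative a held-out window would be.** At 0.20 per year, 2,240 patients give 448 events per arm in 12 months and 224 in six.
- 12 months: SE = √(2/448) × √2.11 = 0.097, so the 95% CI factor is exp(1.96 × 0.097) = 1.21.
- Six months: SE = √(2/224) × √2.11 = 0.137, so the factor is 1.31.

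**Effect of the look-back.** I simulated an extreme case: every intervention patient has at least one ASE in three years, the pool is unselected with mean 0.08 and k = 0.5, and matching uses one of those years only. The ratio in a held-out year inside the look-back is 3.4, while the ratio after enrolment is 1.5. A held-out ratio away from 1 is therefore not a direct estimate of the bias after enrolment.

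**The case against.** The strongest reply has four parts.

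First, the matching set is wider than age, sex and the ASE count. Diagnosis and comorbidities are named and the list is open. This stands, and it governs the size: if these variables bring the control pool to the same underlying rate, the bias vanishes. The article also credits the higher rate to chronic disease as well as to clinical judgement. A reader might put the general-population rate into the formula (μ = 0.08 gives 7.25/3.5 = 2.07), but nothing supports that as the residual mean for diagnosis-matched patients.

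Second, a reader might infer that the design could just as easily create a false benefit through enrolment at a clinical peak. The documents support this less well. Table 1 accepts events up to three years old and stable patients with lasting features such as frailty, and worsening is only one sign among several. It remains possible, because the life-expectancy exclusion and the condition of 12 months of care are stated for intervention patients only.

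Third, a reader might conclude that no planned analysis could reveal the problem. That cannot be known. Covariate adjustment and further sensitivity analyses are promised without detail, and a statistical analysis plan may exist that is not shown.

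Fourth, the Discussion already concedes that matching may leave residual differences. That is fair, but it does not repair the Matching section, which states the opposite inference as the reason for its selection rule.

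**Conclusion.** The point holds in a limited form. Choosing a method by balance is sound practice. Stating that this minimises selection bias is not, because the selection here uses information that the matching variables may not hold, and balance on a noisy outcome count cannot show what is left.

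The size is conditional. With shape 0.5, a residual pool mean of 0.19, 0.18 or 0.15 against 0.20 gives a ratio of about 1.04, 1.08 or 1.24 with no effect. The documents do not show which of these applies. The first costs some power; the last hides the planned effect completely. The model assumes gamma-distributed rates and exact matching on 12 months. The probabilities of a significant benefit also take the stated 82% at face value.

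**What to change.** 1. Replace the statement on selection bias with wording that balance addresses measured variables only.
2. Before matching, apply claims-based versions of the intervention eligibility rules to the control pool: chronic care fee billing, continuous treatment in the practice, and prior ASE where observable. Data from January 2024 cover 24 months before the first enrolments and at most 33 months before the last (end of September 2026), so the three-year look-back can be reproduced only in part.
3. Keep balance as the criterion for choosing the method. For the chosen method, run a second match on one pre-period window only, and report the ASE rate ratio between the groups in a held-out pre-intervention window with a cluster-adjusted 95% CI. Present it beside the primary result as a diagnostic that limits the causal conclusion. It should be neither a pass/fail rule nor a way to pick the method, because choosing the ratio nearest 1 would partly select on noise.
4. Base any difference-in-differences sensitivity analysis on a baseline window that was not matched on. Matching equalises a matched baseline, so the analysis would correct little.

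The cost is a change of wording, a filter on the control pool and one extra matching run on data already requested. The downside is that the held-out ratio is imprecise (95% CI factor about 1.2 for 12 months and 1.3 for six) and partly reflects the events that made patients eligible. Both limits must be stated with the result.
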